### Randomization and blinding

The study has a double-blinded design. Neither the participant nor the outcome assessors will know whether the participant is receiving VR-based cognitive remediation or VR control treatment (details below). At inclusion, participants are informed that they will be randomized to one of two types of VR training programmes which both involve weekly sessions with a therapist. To uphold the blinding, participants are not provided with any further details regarding the VR-based cognitive remediation and control treatment until after randomization. Participants are randomized upon full completion of the baseline assessment with allocation being carried out by the first author using the automated randomization module in the online Research Electronic Data Capture (REDcap) system based on an uploaded blocked randomization list created online using Sealed Envelope Ltd. 2022 [64]. Participants will be randomized using a 1:1 allocation in blocks of varying size from 4-8, and we will stratify randomization with age (< or ≥ 35 years) and diagnosis (MD vs. PSD) to ensure equal distribution in the two groups. To avoid any predictability in the randomization process, the list detailing the randomized blocking sequences is kept inaccessible to the first author who enroll and randomize the participants. The participants will be instructed not to disclose any information concerning their treatment during outcome assessments and under no circumstances will the allocation be revealed to the outcome assessors. Outcome assessors will be asked to note whether the blinding was compromised during the assessment. The first author who undertakes the statistical analyses will be blinded with respect to group assignments when conducting the primary and secondary outcome analyses.

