### Procedure

Upon their first visit at the Copenhagen Affective Disorder Research Centre (CADIC) or Department of Psychology, University of Copenhagen, participants are informed about the project and provide written informed consent, after which they undergo an eligibility assessment. The first author is responsible for recruitment and conducting the first visit during which the informed consent is obtained. After inclusion, the baseline assessments are scheduled and completed over 2 days, 1 to 5 days apart for practical reasons and to avoid attrition.

On day 1, the participant is assessed with a novel VR cognition test of daily life cognitive skills and a comprehensive neuropsychological test battery (see details under ‘Outcome measures’). Participants also complete questionnaires concerning subjective cognitive complaints, quality of life, and general acceptance of VR technology. Daily life functioning is assessed using a clinician-rated interview and a performance-based assessment. Participants with MD undergo mood ratings with the HDRS-17 and YMRS. For participants with PSD, positive symptoms are assessed using the Scale for the Assessment of Positive Symptoms (SAPS) [62], and negative symptoms are assessed using the Brief Negative Symptom Scale (BNSS) [63]. Finally, self-reported sleep quantity and quality in the past 3 days are recorded. At the Copenhagen University Hospital, Rigshospitalet, participants then undergo a functional magnetic resonance imaging (fMRI) scan encompassing a spatial working memory N-back task, a word encoding paradigm in which participants must encode and subsequently recognize words of typical household items, a resting state, and a structural scan.

On day 2, participants’ ability to perform daily life tasks is assessed with the Assessment of Motor and Process Skills (AMPS) [55] by an AMPS-certified occupational therapist in a standardized test kitchen.

The VR cognition test, neuropsychological assessments, questionnaires, clinical symptom ratings, assessments of functioning (including AMPS), and fMRI scan are repeated within 2 weeks after treatment completion (primary outcome assessment time). All assessments except for the fMRI scan are repeated 3 months after treatment completion to assess durability.

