#### Data management and monitoring

All personal information will be obtained at the eligibility assessment or from patient records in cases where participants are unable to provide the needed information. Pseudo-anonymized data from the neuropsychological tests, virtual reality test, questionnaires, interviews, and functional assessment will be registered in the REDcap database, which meets requirements from the Danish Data Protection Agency. Data quality is ensured by score range restrictions on values for all outcomes, and all data for the primary and secondary outcome measures will be double-checked by the first author. Signed consent forms as well as a list that matches participant ID numbers with personal information are kept separate from pseudoanonymized data. The list matching participants’ personal information with their ID number will be deleted and consent forms maculated 10 years after study completion. At this point, all data will be completely anonymized. All trial authors will have access to the final trial data set. If a participant is excluded from or withdraws from the study, the reason for exclusion will be documented in REDcap, along with information regarding any adverse events.

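### Blinding of the analyst is not achievable as described, because the first author who is to analyse blind also carries out the allocation

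*Protocol article*

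**What the plan says.** Four statements in the protocol article describe what the first author does.

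- Procedure: "The first author is responsible for recruitment and conducting the first visit during which the informed consent is obtained".
- Randomization and blinding, on assignment: participants are randomised once baseline is complete, with "allocation being carried out by the first author using the automated randomization module".
- Data management and monitoring: "all data for the primary and secondary outcome measures will be double-checked by the first author".
- Randomization and blinding, last sentence: "The first author who undertakes the statistical analyses will be blinded with respect to group assignments when conducting the primary and secondary outcome analyses".

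Two protective measures also appear under Randomization and blinding. To prevent predictability, "the list detailing the randomized blocking sequences is kept inaccessible to the first author who enroll and randomize the participants". For those who rate outcomes, "under no circumstances will the allocation be revealed to the outcome assessors". The second measure names outcome assessors only, and no matching rule is given for the first author.

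**The concern.** A person who carries out an allocation would ordinarily learn its result. If that person later fits the models, replacing the arm names with letters gives little protection, because the participants and their assignments are already known. This person has also met the participants at the first visit and gone through their outcome values.

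Blinded analysis protects the choices that remain open once data are in: covariates, the handling of odd values, the definition of analysis sets, and the reading of borderline results. The article presents it as a feature of the trial, and later reports would be expected to repeat it. If it is not delivered, readers will credit the results with a safeguard that was not in place.

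**Working it through.** No arithmetic decides this point. The check sets the role statements side by side and asks whether any stated measure separates knowledge of allocation from the analysis.

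**1. Who knows the participants?** The first author, through recruitment and the first visit (Procedure).

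**2. Who makes the assignments?** The first author, in the REDCap module (Randomization and blinding). The text does not say what the module displays. That the assigned arm is seen is an inference from the role, though a strong one. The two programmes also differ openly in schedule: two therapist sessions a week plus home VR training in one arm, one session a week in the other (intervention and control treatment sections). Someone close to the running of the trial could recognise the arm even if the display were masked.

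**3. Who handles participant-level outcomes?** The first author double-checks the primary and secondary data (Data management and monitoring). This does not unblind by itself. It does let someone who knows assignments connect them with individual outcome values. The data are held under participant IDs, and a separate list linking IDs to persons is kept until 10 years after study completion.

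**4. Who analyses?** The first author, described as blinded for the primary and secondary outcomes.

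**5. Does any stated measure break the chain from step 2 to step 4?**
- Hiding the block list: no. Its stated purpose is to prevent prediction. It conceals the next assignment and leaves past ones known.
- The non-disclosure rule: no. It is written for outcome assessors.
- Masked module output, recoded arms, new IDs, or an independent analyst: none is described.

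**6. How many participants are affected?** The planned total is 66 (Sample size and power calculation), and the article gives allocation to the first author without exception. By September 2023, 35 had been included (Trial status and dissemination), which leaves 66 − 35 = 31 still to be included at that date. Randomisation follows completion of baseline, so slightly fewer than 35 may have been allocated by then. Handing the allocation step to someone else from that date would therefore help at most about half of the sample.

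**The case against.** The strongest reply is that the article neither describes nor rules out a masking step. A colleague could supply a file with coded arms and fresh IDs, and knowing past assignments would not then directly reveal which code is which. Such detail is often left to a full protocol or analysis plan, and neither is shown. This stands to the extent that the promise could be partly rescued. It does not remove the conflict, because the article itself gives allocation and blinded analysis to one person and claims the blinding without qualification.

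A second reply is that the room for bias is limited. The primary test is self-administered, the composite is defined as the mean of five z-transformed subtests, linear mixed models are named, every randomised participant is analysed without ad hoc imputation, and data entry is range-restricted. This also stands in part. It narrows the analyst's discretion but leaves covariates and data corrections open.

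A reader might infer several stronger things that the article does not support.

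- *That blinding is impossible under any arrangement.* Masked output, or recoding of both arms and IDs by someone else, could help.
- *That one known participant-arm pair always breaks an A/B code.* This holds only if the file keeps IDs or values that the analyst can match to a person.
- *That blinded data checking was promised and is missing.* The article says only that the data are double-checked.
- *That assessor blinding or allocation concealment fails.* Nothing in the text shows either.

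**Conclusion.** The point holds in limited form. The article claims a blinded analysis by the person who carries out the allocations, and the one safeguard stated for that person protects only future assignments. Analyst blinding is therefore not achievable as described, and the sentence should not stand unchanged.

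The gap covers all 66 planned allocations in the sense that no exception is stated. It is not proof that the analyst will in fact know all 66 arms at the time of analysis. Two assumptions carry the conclusion: that carrying out the allocation in REDCap reveals the arm, and that no undescribed masking step separates allocation from analysis. No bias can be estimated from the document, and none is shown to have occurred.

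**What to change.** 1. Finalise and date-stamp the analysis syntax for the primary and secondary outcomes before allocation is merged with outcome data.
2. Complete the double-check and lock the primary and secondary outcome data before the same merge, so that no value can be altered once results by group can be seen.
3. Have an existing team member who has not seen allocations run that syntax on a file with coded arms and new participant IDs, prepared by someone else.
4. Correct the sentence under Randomization and blinding to say who analyses and how masking is achieved.

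If this is not done, delete the sentence and report the analysis as not blinded.

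Moving the allocation step to another person is not enough, because it cannot help participants already allocated. It would also rest on staff roles that the article does not describe.

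The cost is a small reassignment of tasks and a short text change, or else a less favourable blinding statement. This assumes that the team includes someone who has not seen allocations, which the article does not state. Access should be no obstacle, since all trial authors are to have the final data set (Data management and monitoring).

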### Study setting

The CAVIR trial will be conducted at CADIC, Psychiatric Center Copenhagen, Frederiksberg Hospital, and at the Department of Psychology, Copenhagen University, Denmark. MR scans are conducted at the Copenhagen University Hospital, Rigshospitalet, Copenhagen, Denmark.

### Intervention: virtual reality-based cognitive remediation

The VR-based cognitive remediation intervention is primarily strategy based and comprises individual psychoeducation combined with training of cognitive skills in VR daily life scenarios that helps participants practice and transfer learned cognitive strategies. The scenarios and cognitive strategies have all been chosen and developed based on feedback from participants in our proof-of-concept study [44], our previous group-based CR intervention [25], and with input from students with MD or PSD attending the School for Recovery at Psychiatric Center Copenhagen [65] who participated in a focus-group interview. These steps were taken to ensure the highest possible relevance of the intervention in line with recommendations to include expert-by-experience knowledge [45]. Additionally, the scenarios were developed in collaboration with clinicians at the Copenhagen Affective Disorder Clinic. All scenarios were pilot tested for feasibility in a minimum of three test participants and optimized further based on their feedback.

The short-term, intensive programme has a duration of 4 weeks and involves two weekly 2-h training and bridging sessions with a therapist accompanied by additional between-session VR training at home and homework assignments consisting of cognitively challenging daily life tasks. The main component of the intervention is the fully immersive VR training platform in 360° Oculus Quest 2 software [66]. The platform includes four daily life scenarios in which patients have consistently reported that they often experience cognitive difficulties: 1) a kitchen scenario focusing on planning and cooking a meal, 2) a supermarket scenario focusing on grocery shopping, 3) a restaurant scenario focusing on remembering names and personal information, and 4) an office scenario focusing on planning, initiating, and completing work assignments (see Fig. 2). Each scenario has a duration of 15–30 min per level and comprises multiple subtasks targeting different types of daily life cognitive skills (e.g. remembering items from a shopping list). All scenarios are designed based on an adaptive learning methodology to ensure optimal learning and motivation [21, 67]. Specifically, there are between three to six levels of varying difficulty in the scenarios, and participants require an 85% success rate to advance to a more challenging level [67]. Participants are introduced to a new VR scenario each week, starting with the kitchen scenario (low VR skill level requirement) and finishing with the office scenario (high VR skill level requirement). The scenarios all include an introductory module and CR strategies embedded directly in the VR environment that are presented to the participant before they complete the tasks.

**Fig. 2 Fig2:**
[figure not shown]
Virtual reality training environments

The virtual reality training is supported by a psychoeducational programme that focuses on the application of learned cognitive strategies in daily life. The programme is designed to match the content of the weekly VR training scenario and covers the following themes: meta-cognition and seeking out cognitive challenges (week 1), strategic learning and memory strategies (week 2), verbal memory and sustaining attention (week 3), and organizing and prioritizing (week 4). The first session also introduces the structure of the treatment and focuses on individual goal setting, including identification of cognitive strengths and weaknesses based on the screening carried out during the eligibility assessment. Each session consists of a short presentation of the theme of the day followed by training in VR (2 × 30 min) and a discussion of how the VR training is related to the individual experiences and goals of the participant. Each session ends with identifying cognitively challenging tasks for the participant to carry out between sessions (e.g. cooking a meal, going shopping without a list, remembering conversation, reading, or organizing and completing tasks at home). Participants then take a head-mounted display (HMD) home to conduct between-sessions VR training (2 × 30 min of home training per week). Treatment completion is defined as 80% attendance corresponding to full completion of six out of eight in-person training sessions. When a participant is unable to attend a scheduled session, the therapist will help the participant catch up on the session’s content through additional at-home training or by extending the subsequent treatment session. The VR training at home is recorded for subsequent evaluation of feasibility. At the final session, participants return the HMD, and a discussion takes place on whether and how they benefited from the intervention, along with encouraging them to keep practicing learned skills. They also receive a leaflet with information from the training sessions.

### Virtual reality control treatment

Participants in the control group attend a weekly 2-h session with a therapist during which they complete different VR games that are available through the Oculus Quest games store [68]. The chosen games involve no direct training of cognitive skills, such as planning skills or strategic learning, but merely involve simple reaction time and interaction with an entertaining environment that is meaningful to the participant. At the session, participants also complete alternative versions of the same VR training scenarios as the training group (i.e. kitchen, supermarket, restaurant, and office) in which the training elements (i.e. strategies, adaptive difficulty level, and feedback) have been removed. These control sessions are conducted for three reasons: (i) to assess whether a potential effect on the VR cognition test (primary outcome measure; see details below) reflects a therapeutic effect rather than simple perceptual habituation to VR environments (i.e. becoming better at using and interacting with VR), (ii) to control for the nonspecific effects of meeting weekly with a therapist, and (iii) to blind study participants in both groups so that all participants have the impression of training their cognitive functions and daily life cognitive skills in VR. To ensure engagement in the control group, participants are asked at the end of each session to complete questionnaires evaluating their experiences with the VR games and scenarios.

### Outcome measures

#### Virtual reality-based assessment of daily life cognitive skills

The effect of the intervention is assessed with a novel VR test of daily life cognitive skills, the Cognition Assessment in Virtual Reality (CAVIR) test [69]. The CAVIR test is an engaging, immersive, and self-administered 360° VR test in a kitchen, where the participant’s cognitive skills related to planning and preparing a meal are assessed [69]. The test has proven high validity, sensitivity, and feasibility for cognitive assessment in MD and PSD [69] and can be considered a more ecologically valid alternative to neuropsychological assessment, as it enables insight into patients’ daily life cognitive skills (i.e. the ICF level of activity/participation) which is the primary target of the intervention. The test has a duration of 15 min and involves five subtasks probing different cognitive skills and underlying cognitive functions: 1) memorizing ingredients from a list (verbal memory), 2) planning the order in which to complete subtasks involved in cooking a meal (executive functions), 3) placing as many correct ingredients as possible in a pot within a time frame (processing speed), 4) memorizing the location of cutlery and flatware in the kitchen cupboards and drawers (working memory), and 5) repeatedly checking the food in the oven in response to a specific combination of cues while ignoring irrelevant stimuli (sustained attention) (for details, see supplementary materials in Appendix B). Importantly, the CAVIR test differs in content from the kitchen scenarios used in the intervention and control treatment, although they all comprise similar subtasks in a VR kitchen environment. Specific differences between the test and training scenarios include the kitchen design and setup (e.g. different interior and placement of items) and test stimuli as different meals are prepared (e.g. different ingredients and visual/auditive cues). The CAVIR test is available in two parallel versions, and participants are assessed with different test versions across assessment points in a counterbalanced design to minimize contamination due to test familiarity.

#### Neuropsychological assessment of cognitive functions

The VR-based cognitive remediation primarily targets daily life cognitive skills, but we also expect that the drill-and-practice component of the intervention will improve underlying cognitive functions (i.e. the ICF level of body functions). Cognitive functions are therefore assessed by a trained research assistant using a broad test battery comprising the following traditional neuropsychological tests: the One Touch Stocking of Cambridge (OTS), the Spatial Working Memory test (SWM) and the Rapid Visual Information Processing (RVP) from CANTAB (Cambridge Cognition Ltd.), the Rey Auditory Verbal Learning Test (RAVLT) [70], WAIS-III Letter-Number Sequencing [71], RBANS Coding and Digit Span [72], verbal fluency [73], and Trail Making Test A and B [74]. Premorbid verbal IQ is assessed with the Danish Adult Reading Test [75].

#### Assessment of daily life functioning

The potential transfer effect of the intervention to daily life functioning will be assessed with the Assessment of Motor and Process Skills (AMPS) [76]. The AMPS is a standardized observation-based occupational therapy evaluation developed to describe and measure a person’s ability to perform activities of daily living (ADL) tasks. When administering the AMPS, the participant is first interviewed about their ADL task performance, to identify standardized ADL tasks that are both relevant to the person and represent a sufficient challenge to the person (from simple to more complex cooking, cleaning, and other household tasks). Next, the participant chooses and performs at least two of the ADL tasks while being observed by an AMPS calibrated occupational therapist. During an AMPS evaluation, two domains of performance are evaluated: ADL motor skills (16 items) and ADL process skills (20 items) (for further details, see Appendix B). Several studies support that the AMPS ADL motor and process ability measures are reliable and valid among persons with psychiatric illness and cognitive impairment [77]. A clinically relevant difference has been determined as ≥ 0.3 logit on the ADL motor or process ability scales [76]. Functioning is also assessed with the UCSD Performance-Based Skills Assessment B (UPSA-B) [78, 79] and the clinician-rated interview Functional Assessment Short Test (FAST) [80].

